### The current study

This study will assess the efficacy of Valued Living, a well-piloted ACT group intervention designed to address the psychological needs of anxious cancer survivors during the transition from cancer patient to post-treatment survivor (the re-entry phase). As noted, this trial addresses a number of limitations from previous trials in re-entry phase cancer survivors, first, by targeting anxious cancer survivors rather than cancer survivors generally; second, by adapting an evidence-based behavioral intervention model (ACT) to address the psychosocial needs of anxious cancer survivors; third, by collaboratively designing the intervention with community providers for sustainability in community-based cancer care settings.

Valued Living will be compared to an enhanced usual care control (UC)*.* This study thus aims to determine whether ACT improves outcomes for anxious cancer survivors beyond any benefits realized by usual care. More specifically, we will evaluate the hypothesis that ACT will improve psychosocial functioning by reducing negative effects such as anxiety symptoms (primary outcome), anxiety disorders, intrusive impact of cancer, fear of recurrence, and depressive symptoms, and by increasing positive effects such as appropriate medical care utilization, sense of life meaning, and vitality, relative to the UC control group. Second, to better understand how the group ACT intervention works, we will explore the active therapeutic processes that predict subsequent improvement in outcomes, including change in experiential avoidance and values-driven behavior.

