#### Usual care control

Usual Care (UC) will consist of mailing each patient a list of oncology support group resources specifically tailored to each geographic area of recruitment. UC participants will also be encouraged to contact their RMCC social worker (or if they are not RMCC patients, the social worker at their cancer care center) for individual support as needed. UC is designed to provide ethical care for anxious cancer survivors using standard social worker time and resources. In both conditions, we will ask participants to report use of outside supportive and mental health resources on their medical trackers (see below) to account for their use in the analyses.

After the 6-month follow-up (i.e., the final assessment point), UC control participants will be offered the opportunity to participate in an ACT group (free of charge), thus maximizing potential study benefits for all patients. The data from these additional groups will not be included in the primary analyses because we risk confounding the data by comparing cancer survivors at different time points from re-entry and screening, and because we expect that not all UC participants will elect to complete the ACT group. By offering ACT to UC control participants as a benefit of follow-up completion, we aim to enhance patient care without confounding the data.

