#### Medical utilization

The *Medical Tracker*, based on previous psycho-oncology studies that have tracked medical utilization [39, 92], has participants track their medical appointments as well as appointments related to mental health and well-being such as support group(s), counseling, and related resources. It tracks the date of the appointment, the reason for the visit, including whether this visit was “related to your experience with cancer?”, the type of provider, whether the visit was a routine/ regular appointment or for a problem, whether they attended the appointment, and if so, how many minutes the appointment lasted. The medical tracker has two purposes: 1) to track attendance at routine cancer-related appointments and initiation of problem-related oncology visits, which serve as secondary outcomes, and 2) to track use of non-study supportive care and mental health care to account for their use in the statistical analyses. A randomly selected 15 to 20% of RMCC patients enrolled in the study will be selected for medical chart review to confirm the information listed by the patient in the *Medical Tracker*. Please note that for ethical reasons, participants will be permitted to pursue psychosocial interventions and support outside of the study; however, we will request that they track this care in their Medical Trackers.

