### Data analytic approach

For Aim 1, we will use multilevel mixed modeling to compare the ACT versus UC control groups on the rate of linear and curvilinear improvement, and at each assessment point, to compare between-group means. We will conduct separate intent-to-treat and intervention completer (“protocol adherent”) analyses. The HADS-Anxiety will serve as the primary outcome, although the other outcomes will be analyzed as well.

For Aim 2, to evaluate the session-by-session measures of active acceptance and values-driven behavior, first, we will assess change slopes over time for each process measure. Then, using time-lagged multilevel models, we will assess the extent to which change in active acceptance predicts subsequent change in values-driven behavior and vice versa, to identify the relationship between these two hypothesized ACT processes over time during the intervention. We will also test whether session-by-session change in each process predicts outcomes at Post and FU. If both putative processes significantly change over time and predict outcomes, then using a multiple mediation framework [103], we will assess which ACT process predicts outcomes more robustly when both processes are compared directly, to evaluate which process primarily drives outcomes.

Each analysis will include the hypothesized predictors as well as potential confounding factors (e.g., use of supportive care external to the study, cancer recurrence, age, gender). We will also conduct exploratory moderator analyses through subgroup analyses and moderation models to identify who most benefitted within each condition.

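### The covariate rule puts outside supportive care, which arises after randomisation and can depend on arm, into the primary ACT versus UC model, so the estimate can drift from the stated question

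*Protocol article*

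**What the plan says.** After describing both aims, the Data analytic approach section of the protocol article sets one covariate rule: "Each analysis will include the hypothesized predictors as well as potential confounding factors". Its examples are "potential confounding factors (e.g., use of supportive care external to the study, cancer recurrence, age, gender").

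The same section defines what the rule governs. For Aim 1, "we will use multilevel mixed modeling to compare the ACT versus UC control groups on the rate of linear and curvilinear improvement", together with between-group means at each assessment. On outcomes, "The HADS-Anxiety will serve as the primary outcome, although the other outcomes will be analyzed as well". On analysis sets, "We will conduct separate intent-to-treat and intervention completer (“protocol adherent”) analyses". None of these is exempted, and no model restricted to pre-randomisation covariates is described.

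Two other sections point the same way. Under Usual care control, participants in both arms will "report use of outside supportive and mental health resources on their medical trackers (see below) to account for their use in the analyses". Under Medical utilization, one of the two purposes of the Medical Tracker is "to track use of non-study supportive care and mental health care to account for their use in the statistical analyses".

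The question the trial sets itself, under The current study, is "whether ACT improves outcomes for anxious cancer survivors beyond any benefits realized by usual care".

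**The concern.** A confounder of a treatment comparison is a common cause of treatment and outcome. Under randomisation, nothing that happens after allocation can be one. Outside supportive care is sought and recorded after allocation, so calling it a confounder in the ACT versus UC comparison is a category error, and adjusting for it has two possible consequences.

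- If the care lowers anxiety and the arms use it to different degrees, adjustment removes a real part of the difference between being offered ACT and being left with usual care.
- If more distressed people seek more care, conditioning on use creates an association between arm and underlying distress that randomisation had removed.

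The two act in opposite directions, so the sign of any error cannot be known in advance. What is at stake is the primary HADS-Anxiety estimate: the adjusted coefficient would describe ACT versus UC at a fixed level of outside care, not benefit beyond usual care as delivered.

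**Working it through.** **Step 1: timing.** Study ethics and integrity places the baseline assessment before randomisation. Medical utilization says participants may pursue outside support while in the study and are asked to track it. Outside care, as recorded, is therefore post-randomisation. For recurrence, the eligibility criteria require no evidence of disease for solid tumours, so recurrence is most naturally a later event, though the article does not say so.

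**Step 2: can outside care depend on arm?** The mailed list of support resources goes to both arms (Valued living intervention), so it does not separate them. Two things do. The prompt to seek individual help from a social worker is stated for UC only, and ACT participants attend seven weekly two-hour groups. Either could change how much other support people use.

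**Step 3: the plan's own figures.** The power section gives n = 50 per arm, d about 0.50 and 88% power at the 3-month follow-up. A plain two-sample normal approximation at an assumed two-sided alpha of 0.05 gives 70.5%. Adding baseline adjustment with an assumed correlation of 0.6 gives 87.8%. The means, variance components and alpha are not printed, so the 88% can be neither confirmed nor faulted. It does not bear on this point; only d about 0.50 is used below, as a yardstick.

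**Step 4: size of the shift.** In a linear model without an arm-by-care interaction, with γ the coefficient of care given arm and p the uptake in each arm,

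adjusted effect − unadjusted effect = γ × (p_UC − p_ACT).

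The shift is zero if uptake is equal or if γ is zero. γ combines the effect of care on anxiety (negative if care helps) with the association from distressed people seeking care (positive).

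I simulated 2 million participants per scenario, allocated 1:1, at a single time point. Anxiety = −0.50 × arm + b × care + 0.6 × distress + noise, with total SD about 1. Care-seeking propensity correlates g with distress and is cut to give the stated uptake. All of these values are assumptions except the 1:1 ratio and the −0.50, which takes its size from the plan's d. Selected results in SD units:

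| Uptake UC/ACT | b | g | Unadjusted | Adjusted | Shift |
|---|---|---|---|---|---|
| 40/40% | −0.30 | 0 | −0.500 | −0.500 | 0.000 |
| 40/40% | 0 | 0.5 | −0.499 | −0.500 | 0.000 |
| 40/30% | −0.30 | 0 | −0.470 | −0.500 | −0.030 |
| 40/30% | 0 | 0.5 | −0.499 | −0.450 | +0.049 |
| 50/30% | −0.30 | 0 | −0.437 | −0.497 | −0.060 |
| 50/30% | −0.30 | 0.3 | −0.439 | −0.441 | −0.002 |
| 50/30% | 0 | 0.5 | −0.497 | −0.400 | +0.097 |
| 60/20% | −0.30 | 0 | −0.380 | −0.500 | −0.120 |
| 60/20% | 0 | 0.5 | −0.502 | −0.301 | +0.200 |

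Check against the formula: for 50/30% with b = 0 and g = 0.5, γ = 0.487 and 0.487 × 0.20 = 0.097. For 60/20% with b = −0.30 and g = 0, γ = −0.299 and −0.299 × 0.40 = −0.120.

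A negative shift overstates the total ACT effect and a positive one understates it. In the 50/30% row with g = 0.3 the two mechanisms nearly cancel. Recurrence was not simulated.

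**The case against.** - **Bias is conditional.** A reader might infer that the adjusted estimate is certainly biased. The documents do not support that. They give no uptake figures, and the shift vanishes if uptake is equal or if the two mechanisms cancel. This stands; the claim is that the estimate can be biased.
- **Outside support as part of the comparator.** A reader might infer that outside support is simply what UC consists of. The same mailed list goes to both arms, and the article does not say whether contact with the social worker counts as care external to the study. This also stands. Dependence on arm is plausible but not demonstrated.
- **Recurrence.** Treating it as equal to outside care goes too far. It could mean history before entry. If it means a later event, the article offers no clear route by which seven sessions would change it by the last assessment, about eight months on; its Background calls the evidence linking anxiety to recurrence mixed. If arm does not affect it, it behaves much like a prognostic covariate.
- **The wording is open.** The list is given as examples, a separate analysis plan may fix the final set, and accounting for use could mean description only. This holds for the Usual care control and Medical utilization sections. It does not undo the statement that each analysis will include such factors; a plan that followed that rule would carry the problem over.
- **Aim 2.** In the process analyses, outside care could genuinely confound the link between process and outcome. That may be why the rule was written, but it does not justify extending it to Aim 1.
- **Precision.** The standard error of a simple standardised difference is √(2/50) = 0.20 SD, or √(2/37.5) = 0.23 SD with 25% missing, so a shift of 0.1 SD is about half a standard error. That limits the practical alarm. It does not make a systematic shift of unknown sign acceptable in the primary estimate when avoiding it costs nothing.

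**Conclusion.** The point holds in conditional form. As written, the covariate rule reaches the primary intent-to-treat comparison of HADS-Anxiety and places in it a variable that arises after randomisation and can depend on arm. If uptake differs by arm and outside care affects anxiety or shares causes with it, the estimate can move in either direction away from the total effect that the stated question asks for.

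The size is unknown. Under the assumed inputs it is roughly 0.1 SD either way, which is about 0.1/0.50 = 20% of the design effect, and up to 0.2 SD with an extreme 60/20% split. These figures come from a single-time-point linear model, not from the trial's mixed model, and rest on assumed uptake, care effect and correlation.

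Cancer recurrence belongs outside the primary model on the same principle, with a lower likelihood of bias. Age and gender raise no issue, and no sample-size or power figure changes.

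**What to change.** In Data analytic approach, replace the blanket rule for the primary Aim 1 treatment-effect models with one that limits covariates to variables fixed before randomisation, such as the age and gender already named. Handle baseline HADS-Anxiety once. The power section models baseline as one of four outcome time points; if the analysis does the same, baseline should not also be entered as a covariate.

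Report use of outside supportive care and cancer recurrence by arm. Any model adjusted for either should be labelled exploratory or sensitivity and not presented as the treatment effect. Align the statements in Usual care control and Medical utilization about accounting for outside care, so that they refer to this reporting and to those secondary models.

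The change costs wording only. The Medical Tracker is still needed, and no new data, participants or assessments are required.

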### Studies to date

The few prior anxiety-related interventions have focused on fear of recurrence [29–31] or uncertainty in later survivorship phases [32]. These interventions have taken a cognitive behavioral (CBT) or acceptance-based behavioral approach; randomized trials have shown that they significantly reduce fear of cancer recurrence relative to usual care [33], relaxation training [34], and supportive-expressive group therapy [29, 31]. Thus, CBT and related behavioral approaches have a successful track record of reducing fear of cancer recurrence.

Strong evidence demonstrates that cancer patients with higher levels of anxiety and distress benefit most substantially from psychosocial interventions, relative to their less distressed counterparts [35–37]. Yet except for a single study targeting distressed re-entry phase cancer survivors [38], the interventions developed for re-entry phase cancer survivors [39–48] target general cancer survivors rather than the anxious or distressed survivors most in need of help. This study represents one of the first interventions to focus on cancer survivors who report significant anxiety at reentry. By directing resources towards the cancer survivors most in need of support, and by focusing on the psychological symptom (anxiety) that is most likely to become chronic [3–5], the current approach represents an efficient use of psychosocial resources.

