## Methods/Design

### Study design

This two-armed, prospective randomized controlled trial (RCT) will randomize a minimum of 100 anxious re-entry-phase cancer survivors to group ACT (the Valued Living intervention) or a UC control condition. Participants will be randomized on a 1:1 ratio to ACT or UC using a computer-generated block randomization sequence done by a consulting biostatistician who is otherwise uninvolved in the study. All participants will be assessed at 5 points: baseline (Pre), mid-intervention (Mid), post-intervention (Post), and 3- and 6-month follow-up (3 m and 6 m FU). The Post assessment will occur 1 week after the final group session and the 3 m and 6 m FU will occur 3 and 6 months after Post. In addition, ACT participants will complete process measures before the beginning of group sessions 2, 4, and 6; all participants will complete the process measures during the regular assessments as well.

We considered alternative study designs such as comparing Valued Living to a more active condition, including an alternative psychosocial intervention or single educational session. However, in that this study reflects the first randomized trial of Valued Living, comparison to a staff-demanding condition or one that had not yet been empirically evaluated in the community oncology setting of the study, appeared premature.

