#### Screening measure

The screener aims to identify cancer survivors who are notably anxious about cancer and anxious or depressed in their daily lives. Thus, anxious cancer survivors are eligible even if they also endorse depressive symptoms, reflecting the finding that anxiety and depressive symptoms frequently co-occur among cancer survivors [68] and more generally [69]. The 11 screening items include: 1) a validated 6-item version of the *State-Trait Anxiety Inventory* (STAI; [70]) that inquires about anxiety over the past month. The STAI is the most commonly used measure to identify which cancer patients benefit most from psychosocial interventions [35]. 2) The 4-item *Patient Health Questionnaire* (PHQ-4; [71]) brief measures of anxiety and depression symptoms, selected for brevity, ease of scoring, and consistency with the most recent American Society of Clinical Oncology distress screening guidelines [72]. 3) A 0–10 rating of “your current anxiety about cancer or the effects of cancer treatment”. Based on the Valued Living pilot study [59] and published validation studies, we will use the following as the cutoff for study eligibility: (1) a 5+ on the “anxiety about cancer” scale, which indicates moderate to severe anxiety about cancer *and* (2) a score of 14+ on the brief STAI [73] *or* 3+ on either the anxiety or depression scale of the PHQ-4 [71], which indicates significant anxiety or depressive symptoms in daily life.

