### Power and sample size estimation

To estimate power for the hypothesized effects and to allow for the possibility of missing data in that estimation, we took a multi-faceted approach involving both existing software for power calculation in longitudinal multilevel linear modeling (PINT; [97, 98]) as well as a cutting-edge simulation approach (see [99, 100]). We started with hypothesized means on the main outcome (anxiety) for the treatment group and controls at each of four time points (baseline, post, 3- and 6-month FU). For the treatment group, these hypothesized means come from our pilot data [59]; the UC control group means represent a conservative expectation based on existing data from published studies [101]. Both sets of means show declines (linear and quadratic) over time, with weaker time effects for the control participants. Model specification involved a multilievel linear mixed model, specifying linear and quadratic effects of time (differing by condition), with random intercepts and time slopes for participants within groups. Power was estimated both for mean condition differences at each point in time as well as the condition by linear time interaction. Given the conservative means and the variance components, the hypothesized effect sizes were medium (*d* ~ .50) [102].

With no missing data and sample sizes of *n* = 50 in each group, the power to detect a significant condition by linear time interaction was 90% or greater. The power to detect the mean difference at 3-month FU was 88%. Simulations and PINT power software produced the same results, confirming excellent levels of power.

We then allowed data to be missing at random as a function of time (20% missing at Post; and 25% missing at each 3- and 6-month FU) – a situation that simulations can model [99, 100]. Our estimation that at least 75% of the sample will complete the 6-month FU (i.e., assuming 25% missing data at the final assessment point) is conservative. Even with this level of missing data, the power to detect a significant mean group difference at each Post and FU remained 81% or greater.

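### The exploratory moderator sentence sets its target as benefit within each arm; it should be the ACT-UC difference across moderator levels (minor)

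*Protocol article*

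**What the plan says.** One sentence in the protocol article, at the end of Data analytic approach, deals with moderators. It announces "exploratory moderator analyses through subgroup analyses and moderation models to identify who most benefitted within each condition". It gives two tools (subgroup analyses and moderation models), a status (exploratory) and a purpose (finding who gained most inside each arm). It names no moderator, no condition-by-moderator term and no ACT-UC contrast by subgroup.

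Three other places bear on it:

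- Aim 1, in the same section, is stated as a between-arm comparison: "compare the ACT versus UC control groups on the rate of linear and curvilinear improvement, and at each assessment point, to compare between-group means".
- Power and sample size estimation expects improvement without ACT: "Both sets of means show declines (linear and quadratic) over time, with weaker time effects for the control participants".
- Screening measure selects on high scores. Entry needs 5 or more on a 0-10 rating of anxiety about cancer, "which indicates moderate to severe anxiety about cancer", plus a cutoff on the brief STAI or on a PHQ-4 subscale.

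**The concern.** In a randomized trial, who benefits from a treatment is a question about the difference between arms: does the ACT-UC difference change with the baseline characteristic? Change inside a single arm adds together the natural course after cancer treatment, prognosis, regression to the mean and whatever the assigned condition did. A characteristic that predicts a fall in anxiety in both arms alike is a prognostic factor. Analysed inside the ACT arm alone, it looks the same as a moderator.

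The sentence attaches the word for benefit to within-arm change and so makes that confusion easy. What is at stake is how the exploratory results are described: a list of people said to have gained most could consist of people who improve just as much under usual care. Baseline anxiety is a natural example, because Studies to date reports that cancer patients with "higher levels of anxiety and distress benefit most substantially from psychosocial interventions", and a baseline score is correlated with its own change whether or not anyone is treated.

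**Working it through.** **The plan's own figure.** The article gives no figure for the moderator analyses. The nearest is 88% power for the 3-month mean difference, which does not bear on this point. For scale, d = 0.50 with 50 per arm and two-sided alpha 0.05 (assumed; none is stated) gives 70.5% unadjusted and 87.8% when baseline-adjusted with a correlation of .6. The 88% is therefore attainable, but it cannot be confirmed without the means and variance components.

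**Inputs from the article.** Allocation: "Participants will be randomized on a 1:1 ratio to ACT or UC". Size: "50 in each group". Effect: "the hypothesized effect sizes were medium" (d about .50). Missing data: 25% at 3 and 6 months, leaving 50 × 0.75 = 37.5 per arm.

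**Assumed inputs.** Baseline-follow-up correlation r of .5, .6 or .7; alpha 0.05; equal variances; normal outcomes; no clustering by therapy group. The ACT effect is the same 0.5 SD for everyone, so there is no moderation to find.

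**Step 1: baseline anxiety against its own change, inside one arm.** With unit variances, the covariance of (follow-up − baseline) with baseline is r − 1, and the SD of the change is √(2(1 − r)). The correlation is therefore −√((1 − r)/2). By Fisher's z, the chance of significance is about Φ(atanh|ρ| × √(n − 3) − 1.96). At n = 50, √47 = 6.856:

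| r | \|ρ\| | atanh × 6.856 | Chance of significance |
|---|---|---|---|
| .5 | .500 | 3.77 | Φ(1.81) = 96% |
| .6 | .447 | 3.30 | Φ(1.34) = 91% |
| .7 | .387 | 2.80 | Φ(0.84) = 80% |

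**Step 2: simulation of both analyses.** 3,000 simulated trials per setting gave these flag rates for baseline anxiety:

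| n per arm | r | Within ACT | Within UC | Interaction test |
|---|---|---|---|---|
| 50 | .5 | 96.6% | 96.5% | 4.9% |
| 50 | .6 | 92.1% | 91.6% | 5.5% |
| 50 | .7 | 81.1% | 79.5% | 4.9% |
| 37 | .5 | 89.9% | 89.7% | 5.3% |
| 37 | .6 | 81.9% | 81.0% | 4.8% |
| 37 | .7 | 66.0% | 70.4% | 4.6% |

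UC receives no ACT, yet it flags the same factor about as often.

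**Step 3: a purely prognostic factor, unrelated to baseline anxiety.** With r = .6 and n = 50, a factor that shifts follow-up by 0.2, 0.3, 0.4 or 0.5 SD per SD in both arms is flagged within ACT in 32%, 64%, 86% and 96% of trials. The interaction test stays between about 4% and 5%. By the formula in Step 1, a factor correlating .3 with change gives atanh(.3) × 6.856 = 2.12 and Φ(0.16) = 56%.

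**Step 4: what the correct test can detect.** Split each arm of 50 into halves of 25. The SE of the difference between the two ACT-UC differences is √(4/25) = 0.4 SD. Power is Φ(0.5/0.4 − 1.96) = Φ(−0.71) = 24% for a difference of 0.5 SD, and Φ(1.0/0.4 − 1.96) = Φ(0.54) = 71% for 1.0 SD.

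**The case against.** The strongest reply is that the sentence does not fix a within-arm test. A moderation model in a two-arm trial ordinarily includes a condition-by-moderator term, and the model in the power section already lets time effects differ by condition. The closing words are a purpose clause, which could describe the simple slopes reported after an interaction. The analyses are exploratory, lie outside both aims, and come from a condensed article whose full analysis plan may spell out the model.

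Most of this stands, and it rules out several stronger readings that a reader might infer:

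- *That the interaction will be omitted or each arm fitted alone.* Nothing says so.
- *That within-arm findings will be credited to ACT.* The sentence covers UC equally and makes no such attribution.
- *That baseline HADS-Anxiety is a planned moderator.* It is never named as one. The statement in Studies to date supports enrolling anxious survivors and does not specify a moderator.
- *That 80 to 97% is the error rate of the planned analysis.* The figure comes from assumed correlations and the built-in coupling of a raw change score with its baseline, whereas the article plans multilevel models. The calculation also leaves out selection at screening, which uses the STAI, the PHQ-4 and a 0-10 rating, not the HADS.
- *That the results would decide who is offered the group.* The article does not say this.

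What remains is that the article does state a target and states it badly. Leaving the model specification to an analysis plan is normal, but a purpose clause naming the wrong contrast is not an omission. Aim 1 shows that the authors name a between-arm comparison where they intend one. The exploratory label deals with multiplicity and low power; it does not change which contrast answers the question.

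**Conclusion.** The point holds as a defect in the stated target of one exploratory sentence. Read at face value, it directs at least the subgroup analyses to within-arm change, which cannot distinguish moderation from prognosis or regression to the mean. The protocol's expectation of decline in both arms makes this more than theoretical.

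The numbers show how badly a within-arm reading can mislead: about 80 to 97% false flags for baseline anxiety at 50 per arm (about 66 to 90% at 37), against roughly 5% for the interaction. They are illustrative, depend on the assumptions listed above, and do not predict what this trial will report. Severity is minor: the ACT-UC comparison on HADS-Anxiety is untouched, and the moderation models may already contain the right term.

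**What to change.** Replace the purpose clause at the end of the moderator sentence with wording such as:

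> to test whether the ACT-UC difference varies by baseline moderator, using the moderator-by-condition(-by-time) interaction in the Aim 1 model, with ACT-UC differences and 95% CIs shown across moderator levels; within-arm associations will be reported as predictors of change, not as moderation.

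No baseline HADS-Anxiety covariate should be written into this sentence. The model in the power section treats baseline as one of the outcome time points, so the same measurement would appear on both sides.

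The cost is one clause, with no extra data or participants. The drawback is the low interaction power with 100 participants (24% for a 0.5 SD difference between equal halves, before missing data). A null interaction should therefore not be read as evidence that the effect is uniform, and the analyses should keep their exploratory label.
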